
**Fig. 1 Fig1:**
[figure not shown]
Overview of ACRNaCT trail

For patients with pCR or yp stage I, the study was designed as a non-inferiority trial to compare the long-term outcomes of patients in observational group and those in treatment group with 5-fluorouracil. For patients with yp stage II or III, the study was designed as a superiority trial of 5-fluorouracil in combination with oxaliplatin compared with 5-fluorouracil alone in adjuvant setting. Participants will be allocated 1:1 to an intervention group or a control group after obtaining pathological data. Recruitment initiated in November 2018 and is expected to be completed in December 2020. The trial has been registered in ClinicalTrials.gov on January 30, 2018 (Registration No. NCT03415763), and also, that was registered in Chinese Clinical Trial Registry on November 12, 2018 (Registration No. ChiCTR1800019445).

### Sample size

The sample size is based on the log-rank test. For patients with pCR or yp stage I, the estimated 3-year DFS was 85% for the 5-fluorouracil and 75% for the observation arm. With 80% power and probability errors of 5%, the upper limit of the two-sided 95% confidence interval (95% CI) of the hazard ratio (HR) will not exceed 1.6. Almost 192 patients will be required in each study group. For patients with yp stage II or III, the estimated 3-year DFS was 55% for the 5-fluorouracil alone and 67% for 5-fluorouracil in combination with oxaliplatin arm. With 80% power and probability errors of 5%, approximately 190 patients will be required in each study group.

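### Part 1: 192 patients per arm do not give 80% power for the stated non-inferiority rule (HR margin 1.6) on a 3-year horizon, and the stated DFS rates contradict that margin

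*Protocol article*

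**What the plan says.** Study design and participants (protocol article) sets the aim for the better-prognosis stratum: "For patients with pCR or yp stage I, the study was designed as a non-inferiority trial", comparing observation with 5-fluorouracil. Allocation is 1:1. On timing it says: "Recruitment initiated in November 2018 and is expected to be completed in December 2020".

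The Sample size section gives the calculation. The method is fixed first: "The sample size is based on the log-rank test". The planning rates follow: "the estimated 3-year DFS was 85% for the 5-fluorouracil and 75% for the observation arm". Power is 80% and error 5%. The success rule is that "the upper limit of the two-sided 95% confidence interval (95% CI) of the hazard ratio (HR) will not exceed 1.6". The result is "Almost 192 patients will be required in each study group".

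The section gives no event count and no true hazard ratio at which the 80% is meant to hold. The Outcomes section makes 3-year DFS primary and lists 5-year DFS as secondary.

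**The concern.** The section states almost every input needed to check its own result, and the result does not follow. An HR margin of 1.6 judged by a two-sided 95% interval is demanding: the information comes from events, and a population with 85% 3-year DFS produces few of them. The only pair of rates given also implies an HR above the margin, so as written the trial is planned around a truth in which observation is unacceptably worse.

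Part 1 asks whether chemotherapy can be left out. If observation and 5-fluorouracil are in fact equivalent, the chance of showing it is well below the advertised 80%. A reader who trusts that 80% could take an upper limit above 1.6 as evidence that 5-fluorouracil is needed, when too few events would explain it equally well.

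**Working it through.** **Inputs.** From Sample size: log-rank framework, 3-year DFS 85% (5-fluorouracil) and 75% (observation), 80% power, margin 1.6 on a two-sided 95% interval (one-sided 2.5%), 192 per arm, so 384 in total. From Study design and participants: 1:1 allocation and November 2018 to December 2020, about 26 months. Assumed here because the article does not state them: true HR 1 (the usual planning value for non-inferiority), exponential DFS, uniform accrual, no losses.

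**Step 1: events required.** D = 4(z0.975 + z0.80)² / (ln 1.6)² = 4(1.960 + 0.842)² / 0.470² = 142.1.

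**Step 2: can 192 be reproduced from the stated rule?** Patients per arm = D / (2 × event probability).
- Exactly 3 years per patient at 85% DFS: event probability 0.15, so 142.1 / 0.30 = 474 per arm.
- All follow-up to 3 years after the last patient: λ = −ln(0.85)/3 = 0.0542 per year; with accrual A = 26/12 = 2.167 years, event probability = 1 − [exp(−3λ) − exp(−5.167λ)] / (Aλ) = 1 − (0.850 − 0.756)/0.1174 = 0.198. This gives 142.1 / 0.396 = 359 per arm.

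The stated figure of 192 is not reproduced under either reading.

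**Step 3: power with 192 per arm at true HR 1.** Power = Φ(½√D × ln 1.6 − 1.96), with D = 384 × event probability.

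| 3-year DFS, both arms | 3 years per patient: events, power | 26-month accrual + 3 years: events, power |
|---|---|---|
| 85% | 57.6, 43% | 76.0, 54% |
| 80% | 76.8, 54% | 100.3, 65% |
| 75% | 96.0, 63% | 124.0, 74% |

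Worked example for the first cell: ½ × √57.6 × 0.470 − 1.96 = 1.784 − 1.960 = −0.176, and Φ(−0.176) = 0.43. Simulating the Cox analysis (4,000 runs per scenario) gave 45% and 53% for the 85% row, 54% for 80% with 3 years each, and 64% and 73% for the 75% row.

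**Step 4: what this means for the success rule.** At an observed HR of exactly 1.00 the upper limit is exp(1.96 × 2/√D). With 57.6 events this is 1.68, which fails. With 76 events it is 1.57, which passes narrowly.

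**Step 5: the article's own rates.** 85% against 75% implies HR = ln 0.75 / ln 0.85 = 1.77. With 76.8 events (384 × 0.20), power = Φ(½ × √76.8 × (ln 1.6 − ln 1.77) − 1.96) = Φ(−2.40), about 1%.

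**Step 6: longer follow-up.** At 85% DFS in both arms and true HR 1, following everyone to 5 years after the last patient gives about 107.7 events and power of about 68%.

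**The case against.** The best defence is that any power figure is conditional. The article states neither a true HR of 1 nor 85% DFS in both arms. No section says the HR is to be cut at 36 months, and the Follow-up schedule runs to at least 5 years. All of this stands. The 43% applies only if later follow-up is discarded, the 474 per arm only with exactly 3 years each, and 43-54% is not a ceiling: equal arms at 75% reach 63-74%. None of these cases reaches 80%.

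A second defence reads the 5% error as one-sided. Power at 85% DFS then becomes 55.5% (57.6 events) or 65.7% (76 events). It passes 80% on the 3-year horizon only with 75% DFS in both arms and accrual plus 3 years (83%), and this reading contradicts the two-sided 95% interval in the same sentence. Under the stated interval, 75% in both arms with 5 years for everyone gives 81%, but that is outside the 3-year endpoint.

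A third is that the article is condensed and an analysis plan may exist. Nothing is alleged to be missing. The stated numbers disagree with each other, and an analysis plan cannot make them agree.

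Two stronger readings are tempting and not supported. A reader might infer that part 1 will most likely end inconclusive even if omission is harmless. At 85% DFS with all follow-up used, power is 54%, so success would be slightly more likely than not. A reader might also infer which wrong formula produced 192. Several different combinations of inputs land near that number, and the document does not show which, if any, was used.

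**Conclusion.** The concern holds as an internal inconsistency. Given the two-sided 95% rule and margin 1.6, 192 per arm does not deliver 80% power on a 3-year horizon at a true HR of 1 for any DFS rate from 75% to 85% in both arms. The range is 43-74%, and 43-54% at the 85% stated for 5-fluorouracil. These values assume exponential DFS, uniform 26-month accrual where later follow-up is counted, and no losses; losses would lower them. The direction of the error is secure, while the exact power depends on the DFS rate and on how much follow-up is used. Separately, the stated 85% and 75% cannot be the alternative for a non-inferiority claim at 1.6, because they already lie beyond it.

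**What to change.** 1. Restate the part 1 power for 192 per arm with its assumptions (true HR, DFS rate in each arm, follow-up used), and give the 142 events that 80% power would need.
2. Reconcile the 85% and 75% rates with the 1.6 margin: say what role the 75% plays and at which true HR the power is claimed.
3. Specify that the primary HR uses all follow-up available at the 3-year analysis, without cutting at 36 months. At 85% DFS this raises expected events from 57.6 to 76.
4. Name the 3-year analysis as decisive. If the HR is updated at the 5-year DFS analysis already planned (about 108 events and 68% power at HR 1 and 85% DFS), label it secondary and supportive, so that it is not a second chance to claim non-inferiority.

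The cost is a less favourable stated power and some rewording. No extra patients are required.

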### Randomization process

The minimization technique will be used in the current trial. Stratification factors are age, yield pathological stage and distance from tumor to the anal verge. Patients will be randomly assigned using a central randomization system without masking.

### Neoadjuvant radiotherapy

Preoperative radiotherapy will be consisted of 50–50.4 Gy in 25–28 fractions (1.8–2 Gy), 5 fractions/week. Intensity-modulated radiation therapy will be conducted for the whole pelvis.

### Concurrent chemotherapy

Capecitabine is administrated concurrently with radiotherapy from day 1 to day 5. Patients receive capecitabine (825 mg/m^2^) orally. Alternatively, irinotecan and capecitabine are delivered concurrently with radiotherapy. Patients receive capecitabine (625 mg/m^2^) orally in combination with weekly irinotecan for five consecutive weeks according to the UGT1A1/28 genotype (days 1, 8, 15, 22, and 29). The dose of weekly irinotecan is 80 mg/m^2^ in patients with the *1*1 genotype and 65 mg/m^2^ in those with the *1*28 genotype.

### Consolidative chemotherapy

Consolidative chemotherapy in form of XELOX (capecitabine and oxaliplatin) or XELIRI (capecitabine and irinotecan) is performed for three cycles for 3 weeks after completion of chemoradiotherapy. XELOX (oxaliplatin (130 mg/m^2^) as a 2-h infusion on day 1, followed by capecitabine (1000 mg/m^2^) twice daily for 14 days every 3 weeks) is delivered if patients receive capecitabine. XELIRI (irinotecan (200 mg/m^2^) on day 1, followed by capecitabine (1000 mg/m^2^) twice daily for 14 days every 3 weeks) is delivered if patients receive capecitabine in combination with weekly irinotecan.

### Resection

Patients will undergo restaging 2 or 3 weeks after completion of neoadjuvant CRT. Surgery will be undertaken following principles of TME for patients who are appropriate for undergoing resection. For patients who have locally unresectable disease, additional chemotherapeutic cycles are needed. Alternatively, chemotherapy regimens can be changed. Watch-and-wait nonoperative approach is not recommended for clinical complete responders in terms of high-risk of recurrence. For patients who refuse undergoing surgery, the risk of relapse will be informed. These participants will not be excluded from our study and sustained clinical complete response for 12 months or longer should be reached under intensive surveillance.

### Adjuvant chemotherapy

According to postoperative pathological stage, patients with pCR or yp stage I will be randomly assigned (1:1) into two groups of observation and ACT with 5-fluorouracil. Patients with yp stage II or III will also be randomly assigned to (1:1) the treatment groups receiving either 5-fluorouracil or 5-fluorouracil plus oxaliplatin as ACT. The use of a course of three cycles of ACT is recommended. In 5-fluorouracil group, patients daily receive capecitabine (1250 mg/m^2^) twice for 14 days every 3 weeks orally. In 5-fluorouracil plus oxaliplatin group, adoption of XELOX (oxaliplatin (130 mg/m^2^) as a 2-h infusion on day 1, followed by daily capecitabine (1000 mg/m^2^) twice for 14 days every 3 weeks) or mFOLFOX6 (oxaliplatin (85 mg/m^2^), leucovorin (400 mg/m^2^), and fluorouracil (400 mg/m^2^) followed by continuous infusion of fluorouracil (2400 mg/m^2^) for 46–48 h, repeated every 2 weeks) is optional.

### Follow-up

History, physical examination, tumor markers test, ultrasound imaging of abdomen and pelvis, and radiography of chest will be carried out every 3 months for the first 2 years and every 6 months thereafter. Abdominopelvic CT or MRI and CT scan of chest will be conducted annually. Colonoscopy will be scheduled at 1, 3, and 5 years for post-treatment surveillance.

### Outcomes

The primary endpoint is 3-year DFS and the secondary endpoints are 3- and 5-year OS, 5-year DFS, and the rate of local recurrence and adverse events resulted from CRT and patients’ quality of life. DFS is calculated from the date of surgery to the date of recurrence. OS is defined as the time from surgery to death.

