### Statistical analysis

Continuous measures will be compared using the Wilcoxon rank-sum test. Chi-square or Fisher’s exact test will be utilized to compare categorical variables. The DFS and OS will be estimated using the Kaplan-Meier method. The Cox proportional hazards model will be employed to identify the prognostic factors. No interim analysis will be planned as well.

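### The primary endpoint is called disease-free survival but counts only recurrence, so deaths without recurrence drop out and the more intensive arm can look better than it is

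*Protocol article*

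**What the plan says.** Under Outcomes, the protocol article sets the endpoints: "The primary endpoint is 3-year DFS and the secondary endpoints are 3- and 5-year OS, 5-year DFS". The two time-to-event definitions follow. For the primary endpoint: "DFS is calculated from the date of surgery to the date of recurrence". For survival: "OS is defined as the time from surgery to death". No other section adds death to DFS.

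Statistical analysis gives one estimation method for both: "The DFS and OS will be estimated using the Kaplan-Meier method". It has no rule for a death without recurrence and no competing-risk method. Sample size states: "The sample size is based on the log-rank test".

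Randomisation comes after surgery. Study design and participants says: "Participants will be allocated 1:1 to an intervention group or a control group after obtaining pathological data". Adjuvant chemotherapy agrees for the first part: "According to postoperative pathological stage, patients with pCR or yp stage I will be randomly assigned (1:1) into two groups". Resection says of patients who decline surgery: "These participants will not be excluded from our study".

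**The concern.** The label and the definition do not match. DFS by name asks whether the patient is alive and free of disease; the stated definition asks only whether disease has come back. A patient who dies of toxicity or another cause without recurrence is not a failure under the stated rule.

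This matters because both comparisons set more treatment against less: capecitabine against observation, and a fluoropyrimidine plus oxaliplatin against the fluoropyrimidine alone. Any treatment-related deaths would fall mainly in the more intensive arm, and leaving them out favours that arm.

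- **yp II/III part (superiority).** The omission pushes towards the trial's positive conclusion.
- **pCR/yp I part (non-inferiority of observation).** It makes the 5-fluorouracil comparator look better, so non-inferiority becomes harder to show.

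In neither part can the primary endpoint show net benefit.

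**Working it through.** **Step 1. The text.** Outcomes gives DFS one start (surgery) and one event (recurrence). OS has the same start and the event death. Since the two definitions stand together and only the second names death, the plain reading is that death is not a DFS event. Censoring of such deaths is an inference from the Kaplan-Meier method; the article does not state it.

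**Step 2. Expected events by 3 years, from the rates in Sample size.**
- pCR/yp I: 2 × 192 = 384 patients; 3-year DFS 85% and 75%; mean event probability (0.15 + 0.25)/2 = 0.20; 384 × 0.20 = 76.8 events. If both arms were at 85%: 384 × 0.15 = 57.6.
- yp II/III: 2 × 190 = 380 patients; 3-year DFS 55% and 67%; mean event probability (0.45 + 0.33)/2 = 0.39; 380 × 0.39 = 148.2 events.

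**Step 3. Events left uncounted.** The documents give no rate of death without recurrence. Assume 2–5% within 3 years.
- pCR/yp I: 384 × 0.02 = 7.7 to 384 × 0.05 = 19.2. Against 76.8 this is 10–25%; against 57.6 it is 13–33%.
- yp II/III: 380 × 0.02 = 7.6 to 380 × 0.05 = 19.0. Against 148.2 this is 5–13%.

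These shares hold only if the rates in Sample size describe true DFS. If they describe recurrence alone, the deaths would be additional to these counts, and the sample-size inputs carry the wrong label.

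**Step 4. What the loss means in the yp II/III part.** HR = ln 0.67 / ln 0.55 = 0.670, so |ln HR| = 0.4007. Power = Φ(√D/2 × |ln HR| − 1.96), two-sided 5% (the article does not state sidedness).
- D = 148.2: Φ(2.439 − 1.96) = 68%
- D = 148.2 − 7.6 = 140.6: Φ(2.375 − 1.96) = 66%
- D = 148.2 − 19.0 = 129.2: Φ(2.277 − 1.96) = 62%

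This holds the HR fixed. The gap between 68% and the stated 80% is a separate sample-size matter and is not part of this point. For direction rather than precision: the planned difference is 67 − 55 = 12 points, so each percentage point of excess deaths without recurrence under oxaliplatin would hide roughly 1/12 of it.

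**Step 5. The clock.** Assume randomisation g = 1–3 months after surgery, no events in between, and a constant hazard afterwards. A 3-year rate S counted from randomisation becomes S^((3 − g/12)/3) counted from surgery.

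| From randomisation | From surgery, g = 1 | From surgery, g = 3 |
|---|---|---|
| 55% | 55.9% | 57.8% |
| 67% | 67.8% | 69.3% |
| 75% | 75.6% | 76.8% |
| 85% | 85.4% | 86.2% |

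The 12-point difference in the yp II/III part becomes 67.8 − 55.9 = 11.9 points at g = 1 from these rounded rates (11.8 unrounded) and 69.3 − 57.8 = 11.5 points at g = 3. The levels rise slightly in both arms.

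**The case against.** **The sentence may be shorthand.** The sponsor may intend death to count, and a fuller document may say so. But this is not a detail left out for brevity: the definition is given explicitly, and beside it death is assigned to OS only. If it is shorthand, one line corrects it.

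**Deaths do not vanish from the trial.** OS and adverse events are secondary endpoints, and the data monitoring committee reviews efficacy and toxicity. That is true, but it does not repair the primary comparison.

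**The size is assumed.** This stands. The 2–5% is not in the documents, nor is any excess of toxic deaths under oxaliplatin. Deaths unrelated to treatment, if counted, would also pull the HR towards 1. So the fixed-HR power figures may overstate the loss, and counting such deaths would make non-inferiority easier to show. The case for counting death rests on what the endpoint should mean, more than on power.

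**Stronger readings that a reader might infer are not supported:**
- *That the omission could produce a false claim of non-inferiority.* Leaving out toxic deaths under 5-fluorouracil works against observation, not for it.
- *That starting at surgery biases the treatment effect.* Allocation follows pathology in every arm, so the gap should be similar between arms. It shifts the 3-year level and has little effect on the HR.
- *That patients who decline surgery enter the primary analysis with event-free time built in by selection.* They have no yp stage, so they cannot be allocated under the article's own rules. Resection keeps them in the study but does not say they join a randomised comparison, or that they are counted only after a 12-month response.
- *That the result could not be compared with DFS in other trials.* That depends on outside definitions the article does not give.

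**Conclusion.** The definition is wrong as written and must be corrected: the primary endpoint is time to recurrence under the name of DFS. Its direction is to favour the more intensive arm in both parts, but only in the yp II/III part does that support the trial's positive conclusion.

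The size in Step 3 is illustrative, since it depends on the assumed death rate and on planning rates that describe true DFS. For the pCR/yp I part, the range that follows from the stated 85% and 75% is 10–25%; the higher range needs both arms at 85%.

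The surgery start is a lesser point, worth mending at the same time. The retention of patients without surgery is a matter of reconciliation: neither a DFS nor an OS start date exists for them.

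**What to change.** 1. Define DFS as the time from randomisation to the first of local recurrence, distant metastasis or death from any cause, with a stated censoring rule. Define OS from randomisation.
2. Keep time to recurrence as a secondary endpoint, with death without recurrence treated as a competing event.
3. Confirm that the 3-year rates in Sample size refer to the new definition; if they do not, revise the inputs.
4. Reconcile Resection with Study design and participants, Adjuvant chemotherapy and Outcomes: state that patients without surgery, who have neither a yp stage nor a surgery date, are outside the randomised comparisons and the per-arm numbers.

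**Cost.** Little new data collection should be needed: death dates are required for OS, and the central randomisation system should hold allocation dates. The real cost is a protocol amendment to the primary endpoint during recruitment (begun November 2018, expected to end December 2020) and a check of the sample-size inputs. No interim analysis is planned, so none would have to be reworked.

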### Data collection, management and monitoring

All data will be collected in form of an electronic case report form (eCRF) through an electronic data capture (EDC) system. The data center located at Fudan University Shanghai Cancer Center will be in charge for quality control of study data. The EDC system will check the data automatically and data managers will review the eCRFs regularly. The queries will be sent out to each investigator. The data monitoring committee (DMC) is made up of three surgeons who have no conflict of interest in this study. DMC is responsible for reviewing efficacy and toxicity of intervention independently from the investigators and reporting severe adverse events. No regular auditing is scheduled.

### Statistical analysis

Continuous measures will be compared using the Wilcoxon rank-sum test. Chi-square or Fisher’s exact test will be utilized to compare categorical variables. The DFS and OS will be estimated using the Kaplan-Meier method. The Cox proportional hazards model will be employed to identify the prognostic factors. No interim analysis will be planned as well.

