**Methods:**

According to the postoperative pathological stage, the present study was divided into two parts with different study design procedures. Patients will undergo different therapeutic strategies after collecting data related to postoperative pathological stage. For patients with pathologic complete response or yp stage I, the study was designed as a non-inferiority trial to compare the patients’ long-term outcomes in observational group and those in treatment group with 5-fluorouracil. For patients at yp stage II or III, the study was designed as a superiority trial to compare the oncological effect of oxaliplatin combined with 5-fluorouracil, in addition to 5-fluorouracil alone in ACT. The primary endpoint is 3-year disease-free survival (DFS). Secondary endpoints are 3-year, 5-year overall survival, 5-year DFS, and the rate of local recurrence and adverse events resulted from chemotherapy and the patients’ quality of life postoperatively.

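### The only stated rule for continuous measures is an unadjusted rank-sum test; if quality of life is scored on a scale, that rule leaves any score taken before adjuvant treatment unused and costs precision

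*Protocol article*

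**What the plan says.** The Outcomes section of the protocol article ends its list of secondary endpoints with "patients’ quality of life"; the Methods paragraph of the abstract has "quality of life postoperatively". No instrument, scale, time point or summary measure is given.

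The Statistical analysis section gives one rule for continuous data: "Continuous measures will be compared using the Wilcoxon rank-sum test". Categorical variables go to chi-square or Fisher's exact test, and DFS and OS to Kaplan-Meier. The only regression named is for another purpose: "The Cox proportional hazards model will be employed to identify the prognostic factors".

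Two design features bear on the point. Randomisation comes after surgery: "Participants will be allocated 1:1 to an intervention group or a control group after obtaining pathological data". Allocation is by minimisation: "Stratification factors are age, yield pathological stage and distance from tumor to the anal verge". The stated comparison of continuous measures uses none of these factors.

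**The concern.** The other secondary outcomes are times to an event or rates: "the secondary endpoints are 3- and 5-year OS, 5-year DFS, and the rate of local recurrence and adverse events resulted from CRT". That leaves quality of life as the one listed outcome likely to be a continuous score, and the rank-sum sentence as the one stated rule that would apply to it.

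Patients reach randomisation after chemoradiotherapy, consolidation chemotherapy and surgery. Their scores at that point can be expected to differ widely for reasons unrelated to allocation. An unadjusted test leaves all of that variation in the error term, even where a score from before adjuvant treatment exists and could remove part of it.

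At stake is how well the trial can describe tolerability. In the pCR/yp stage I part, the Discussion expects fewer side effects and less financial burden if chemotherapy is omitted. It does not name quality of life there, but that is one of the places where such a gain could appear. In the yp stage II/III part, the same measure would help to show the cost to patients of adding oxaliplatin. In both parts a reader will want the size of the difference and its uncertainty as well as a p-value.

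**Working it through.** There is no quality-of-life sample size or power in the article to reproduce. The check asks how much precision the stated test gives up.

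**Inputs from the article:** 192 per arm (pCR/yp stage I) and 190 per arm (yp stage II/III), both in Sample size and both derived for DFS; 1:1 allocation.

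**Assumptions, not in the article:** two-sided 5% test; normally distributed scores; one follow-up visit; complete data; true difference d = 0.20 to 0.30 SD; correlation r = 0.3 to 0.7 between the score before adjuvant treatment and the follow-up score.

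**Formulas**

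- Noncentrality of the unadjusted comparison of means: d × √(n/2).
- Rank-sum test: multiply by √(3/π), since its efficiency relative to the t-test is 3/π = 0.955 under normality.
- ANCOVA on the earlier score: divide by √(1 − r²), since the residual variance is (1 − r²) times the unadjusted variance.
- Power = Φ(noncentrality − 1.96).

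**Worked case, n = 192, d = 0.25**

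- Unadjusted: 0.25 × √96 = 2.449; Φ(0.489) = 68.8%.
- Rank-sum: 2.449 × 0.977 = 2.394; Φ(0.434) = 66.8%.
- ANCOVA, r = 0.3: 2.449/0.954 = 2.568; Φ(0.608) = 72.8%.
- ANCOVA, r = 0.5: 2.449/0.866 = 2.828; Φ(0.868) = 80.7%.
- ANCOVA, r = 0.7: 2.449/0.714 = 3.430; Φ(1.470) = 92.9%.

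**Across the range**

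| n per arm | d (SD) | Rank-sum | t-test | ANCOVA r=0.3 | r=0.5 | r=0.7 |
|---|---|---|---|---|---|---|
| 190 | 0.20 | 47.8% | 49.6% | 53.3% | 61.4% | 77.9% |
| 190 | 0.25 | 66.3% | 68.3% | 72.4% | 80.3% | 92.7% |
| 190 | 0.30 | 81.5% | 83.2% | 86.5% | 92.2% | 98.4% |
| 192 | 0.25 | 66.8% | 68.8% | 72.8% | 80.7% | 92.9% |

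**Where the loss comes from.** At 192 per arm and d = 0.25, using ranks instead of means costs 68.8 − 66.8 = 2.0 points. Not adjusting costs a further 4.0 points (72.8 − 68.8) at r = 0.3, 11.9 (80.7 − 68.8) at r = 0.5 and 24.1 (92.9 − 68.8) at r = 0.7. The choice of a rank test is therefore a small matter; the unused earlier score is the larger one.

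**As precision.** Relative to an unadjusted comparison of means, the confidence interval narrows by a factor √(1 − r²) = 0.954, 0.866 or 0.714, that is by 5%, 13% or 29%. Equivalently, 190 per arm acts like 190/(1 − r²) = 209, 253 or 373 per arm.

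**The case against.** The strongest reply is that the article is a condensed account and never says how quality of life will be analysed. The rank-sum sentence is general. It stands beside an equally general one on categorical variables and may be meant for patient characteristics. Instrument, visits, model and reporting are commonly left to the full protocol or the SAP, and neither is shown. This stands in part: the rule reaches quality of life only by elimination, and only if a scale score is analysed. It does not remove the point, because what is questioned is the one method the article states for such data.

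It is also fair that nothing here is an error of validity. An unadjusted rank-sum test is a legitimate comparison of randomised groups, and with skewed or heavy-tailed scores it can do better than an analysis of means. The gain from adjustment is modest at r = 0.3. The endpoint is secondary and was not used for sizing.

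Two stronger readings are tempting, and the document supports neither.

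- A reader might infer from the Follow-up section that no quality-of-life score is planned before adjuvant treatment. That section describes oncological surveillance: "History, physical examination, tumor markers test, ultrasound imaging of abdomen and pelvis, and radiography of chest will be carried out every 3 months", and so on. It lists no adverse-event assessment either, although adverse events are a secondary endpoint, so absence from it shows nothing. The abstract's reference to the postoperative period is compatible with a score after surgery and before adjuvant treatment.
- A reader might infer that the test rules out any estimate of the difference. A Hodges-Lehmann shift with an interval can accompany it, and nothing in the article excludes that. Such an estimate would, however, still be unadjusted.

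**Conclusion.** The point holds in a limited form. If quality of life is scored on a scale, the only rule that the article states for it is valid but inefficient, because it cannot use a score from before adjuvant treatment. For a 0.25 SD difference the cost is about 6 power points at r = 0.3, 14 at r = 0.5 and 26 at r = 0.7, of which about 2 are due to ranking.

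These figures rest on an assumed difference, an assumed correlation, normality, one visit and complete data. None of these comes from the documents, and bounded or skewed scores may reduce the gain. Whether a score before adjuvant treatment is collected cannot be told from the article, and no claim is made that it is missing. Neither DFS comparison is affected. This is a minor improvement to a secondary endpoint.

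**What to change.** For quality of life, name a model adjusted for the score taken after surgery and before adjuvant treatment as the main analysis: ANCOVA for a single follow-up visit, or a repeated-measures mixed model if there are several. Report the adjusted between-arm difference with its 95% confidence interval, and keep the rank-sum test as a sensitivity analysis.

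Confirm that the questionnaire is completed at randomisation, before adjuvant treatment starts. If it is not, add it at that point in all arms.

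The cost is a few sentences of analysis text and at most one questionnaire per patient. Sample size, treatment and the surveillance visits do not change. The downside is small: patients already randomised without that score need a stated method for a missing baseline.
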